### Trial conduct

#### Index case identification

Adult MDR-TB index cases are identified via routine National TB Programme TB clinics/hospitals or via other (e.g. laboratory-based) surveillance methods and assessed for eligibility as index cases (Table 2). Adults are approached at their local clinic/hospital or at home to provide consent for collection of their TB episode data and a sputum sample, and for permission to conduct a home visit to enumerate all household members and eligible child contacts (Fig. 1).

**Table 2 Tab2:** Inclusions and exclusion criteria for adult index cases and child trial participants

Adult index case inclusion criteria	Child participant inclusion criteria	Child participant exclusion criteria
1. Age ≥ 18 years 2. Bacteriologically confirmed pulmonary TB diagnosed from a sputum sample within the preceding 6 months 3. Genotypic and/or phenotypic resistance to isoniazid and rifampicin^a^ 4. Written informed consent to provide routine TB episode data 5. At least 1 child household contact aged < 5 years reported to have been residing in the same household as the adult index case in the previous 6 months	1. Child aged < 5 years who is a household contact of an enrolled adult MDR-TB index case diagnosed during the previous 6 months^b^ 2. Primary residence in the household of the adult MDR-TB index case 3. Consent from the parent or legal guardian for the child for HIV testing^c^ 4. Consent obtained from the parent or legal guardian for the child to be enrolled in the study	1. TB disease at enrolment 2. Currently on isoniazid or a fluoroquinolone^d^ for ≥ 14 days 3. Treated for TB in the previous 12 months 4. Known concurrent exposure to an isoniazid-susceptible (including rifampicin-monoresistant) index case^e^ 5. Children with myasthenia gravis or Guillain–Barré syndrome

^a^If only tested by Xpert MTB/RIF or other approved molecular tests, the index case can be included if rifampicin-resistant, without other confirmed DST. Rates of rifampicin-resistant, isoniazid-susceptible TB are very low in this context [58]. Samples found to be rifampicin-resistant will subsequently be confirmed by other molecular testing and/or by phenotypic DST

^b^Children aged < 5 years who are identified as having been living in the same household as an enrolled adult MDR-TB index case at any point during the preceding 6 months are eligible, if the exposure has lasted > 2 weeks

^c^HIV-infected and uninfected children will be included

^d^Levofloxacin, moxifloxacin, ofloxacin or ciprofloxacin

^e^Any child found to have been in contact with an index case who has isoniazid- or rifampicin-susceptible TB will be referred to the local clinic to access preventive therapy, as per WHO guidelines

**Fig. 1 Fig1:**
[figure not shown]
The series of activities conducted by the study team to identify eligible child contacts of multidrug-resistant tuberculosis index cases

#### Household assessment

Following the evaluation of an adult MDR-TB index case, home visits are undertaken and the household contacts enumerated. Comprehensive infection control procedures are followed to protect staff. Screening is conducted in all household contacts to identify those with prevalent TB disease, to rule out additional individuals who may have drug-susceptible-TB and to identify child household contacts who do not have prevalent TB disease and who are eligible for enrolment. Household characteristics and children’s TB exposure are captured using a standard approach [48]. All household members aged ≥ 5 years with suggestive symptoms are referred for TB investigation and TB/HIV care as appropriate.

#### Definition of household

Households are defined using a standard inclusive definition [49]. A household contact is defined as a person who currently lives or lived in the same dwelling unit or plot of land and shares or shared the same housekeeping arrangements as the adult MDR-TB index case, and where there is reported exposure within six months before the index case starting MDR-TB treatment.

#### Screening children for eligibility

Written informed consent from caregivers is obtained to screen for study entry and eligibility (Table 2). Children aged < 5 years who are identified as having been living in the same household as an enrolled adult MDR-TB index case at any point during the preceding six months are eligible, if the exposure has lasted > 2 weeks. Anthropometric measurements are completed, TB symptoms and signs captured, and chest radiographs (CXR), HIV testing and IGRA (QuantiFERON-TB Gold Plus; Qiagen) done. Any children with suggestive symptoms or signs of intrathoracic or extrathoracic TB disease, or with concerning CXR features, are investigated for TB disease (including sampling for bacteriological testing) and are referred for TB care if TB is diagnosed. If any adult is identified with isoniazid- or rifampicin-susceptible TB in the household, then all children in the household become ineligible. Any child found to have been in contact with an index case who has isoniazid- or rifampicin-susceptible TB will be referred to the local clinic to access preventive therapy, as per WHO guidelines. Prevalent TB in child contacts is defined using standard international case definitions for paediatric TB in contact investigation studies (Table 1) which have been harmonised between three international MDR-TB preventive therapy protocols (TB-CHAMP, V-QUIN and the ACTG/IMPAACT PHOENIx trials). CXR findings suggestive of intrathoracic (pulmonary) TB are defined in Table 3.

**Table 3 Tab3:** Chest radiograph features characteristic (‘typical or highly suggestive chest radiograph findings’ of TB in children aged < 5 years, by disease severity status)

Non-severe disease	Severe disease
• Uncomplicated LN disease - hilar or mediastinal nodes, nodes with unilateral airway narrowing, nodes with single lobe bronchopneumonia, nodes with segmental opacification (< 1 lobe) • Isolated Ghon focus • Simple pleural effusion	• Complicated LN disease (airway compression with hyperinflation or collapse or bilateral airway compression) • Expansile pneumonia (involving ≥ 1 lobe) • Ghon focus with cavitation • Miliary TB • Complicated pleural effusion (alveolar disease with effusion, pneumothorax, loculated pyopneumothorax with air-fluid level), loculated pleural effusion • Adult-type cavitary disease • Bronchopneumonic consolidation with or without cavities or visible lymph nodes • Suspected pericardial effusion (cardiac enlargement)

*LN* lymph node, *TB* tuberculosis

#### Child enrolment

Carers/legal guardians of child household contacts are approached; consent is obtained for screening and, if eligibility is confirmed, subsequent enrolment.

#### Randomisation

All eligible contacts in a household consenting to participate are allocated to the same study arm, but participation of all eligible child household contacts is not required for the household to participate. Enrolment of children and randomisation of households into the study is via a centralised web-based system to maintain allocation concealment. Randomisation is stratified by site and households are randomised 1:1 to either levofloxacin or placebo. The randomisation lists are prepared by an individual who is not involved in the day-to-day running of the trial.

#### Interventions

Medications are dosed by pragmatic weight-bands (Table 4). Children randomised to the intervention arm receive levofloxacin at a target dose of 15–20 mg/kg per day once daily for 24 weeks. Although this is the recommended target dose [50], we acknowledge that higher dosages may be needed to achieve the serum concentrations seen in adults when dosed with 750 mg once daily [51]. In addition, as can be seen in Table 4, the use of weight-bands leads to some over-dosing and some under-dosing for children at the boundaries of each weight-band. Children randomised to the control arm receive placebo formulated to look and taste identical to the 250 mg (or 100 mg) levofloxacin dispersible tablet. Drug (and placebo) is being supplied initially as 250 mg tablets. During the course of the trial, a 100 mg dispersible tablet (and placebo) is expected to become available for use in the lower weight-bands.

**Table 4 Tab4:** Weight-bands for levofloxacin (100 mg and 250 mg tablets) and resulting drug exposures

Weight-bands (kg)		Tablets of levofloxacin 100 (n)	Tablets of levofloxacin 250 (n)	Range of resulting dosages (mg/kg)			
				Levofloxacin 100		Levofloxacin 250	
				Min	Max	Min	Max
3	4.9	0.5	0.25	10	17	13	21
5	6.9	1	0.5	14	20	18	25
7	9.9	1.5	0.75	15	21	19	27
10	11.9	2	1	17	20	21	25
12	15.9	2.5	1	16	21	16	21
16	19.9	3	1.5	15	19	19	23
20	24.9		1.5			15	19
25	29.9		2			17	20

Target dosage for levofloxacin is in the range of 15–20 mg/kg

Children in the placebo arm will receive the same number of tablets based on their weight-band

#### Follow-up

Children are seen at 4, 8, 12, 16, 24, 36, 48, 72 and 96 weeks for study visits and at any time that caregivers feel that the child may have developed TB disease or they, or the study team, have other concerns.

### Data collection

The data collected, investigations undertaken and time points at which these are carried out, from the index case, household and child, are indicated in Fig. 2. The TB treatment register at the treating clinic and National Health Laboratory Service database are reviewed by the study team to collect data on the index case. A sputum sample is also collected from the index case for culture, DST and genotyping. At follow-up study visits of the child contacts, anthropometric measurements are recorded and caregivers are asked questions regarding the child. Stool is collected at selected sites for non-mycobacterial microbiology and microbiome analysis. Any child with symptoms or signs suggestive of TB disease, a CXR with features consistent with TB disease, or a CXR with persistent abnormalities despite a course of antibiotics, will be evaluated for TB disease by a clinician and have two respiratory samples (expectorated/induced sputum or gastric aspirate) collected for smear microscopy, GeneXpert MTB/RIF and culture. If the culture is positive, the sample undergoes DST and genotyping.

**Fig. 2 Fig2:**
[figure not shown]
Schedule of evaluations. SCR screening, BL baseline – at randomisation, U/S unscheduled, TB tuberculosis, ALT alanine aminotransferase, BR bilirubin, DST drug susceptibility test, FBC full blood count, IGRA interferon-gamma release assay, WHO World Health Organization. *If intercurrent exposure to an isoniazid- or rifampicin-susceptible TB case, preventive therapy will be offered. **At selected sites only. #Based on clinical indication only – TB symptoms at baseline, or at follow-up: new or persistent symptoms, or CXR changes at any time including endpoint evaluation. HIV testing at 48 weeks will be repeated in HIV-negative participants. If HIV status is already known to be positive at screening, the CD4 count and HIV viral load should be completed at baseline in HIV-infected children. HIV viral load is standard of care in HIV-infected children

### Adverse events

Safety assessments are conducted at each visit during the 24 weeks on treatment and include evaluation of symptoms, signs and laboratory investigations. At every study visit (and at unscheduled visits) a symptom checklist prompts for symptoms relating to possible drug toxicities. All symptomatic patients are evaluated by the study doctor and discussed with the site Principal Investigator. Safety laboratory investigations are performed at baseline and at 8, 16 and 24 weeks and are also performed at unscheduled visits if clinically indicated. AEs (clinical and laboratory) are graded using the 2017 Division of AIDS toxicity grading scale [52]. All AEs are recorded in the child’s notes and reported to the MRC CTU and ethics committees as required within agreed timescales. There are no known drug–drug interactions between levofloxacin and antiretroviral drugs used to treat children living with HIV [42] and a recent evaluation of long-term levofloxacin use in children with MDR-TB found no evidence of cardiotoxicity or QTc prolongation [53].

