There is strong evidence for the efficacy of isoniazid to reduce the risk of progression to TB disease in child and adult contacts of people with drug-susceptible TB [21, 22]. Isoniazid monotherapy, given daily for six months, is therefore recommended by the WHO in children aged < 5 years and HIV-infected individuals, regardless of age, following exposure to infectious drug-susceptible TB [5, 21–24]. However, the WHO does not currently recommend any specific drug regimen for the contacts of people who are living with infectious MDR-TB. No randomised controlled trials have been completed to assess the efficacy of any regimen to prevent MDR-TB [25], but a recent systematic review and meta-analysis of multiple observational studies of MDR-TB preventive therapy concluded that although the results should be interpreted cautiously, a number of different regimens were associated with a reduction in the risk of subsequent TB disease and were cost-effective [26]. Our primary hypothesis is that levofloxacin, given daily for six months, will protect children exposed to MDR-TB from developing TB disease. We also hypothesise that this treatment will be well tolerated, safe and cost-effective.

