#### Choice of intervention regimen

We considered a wide range of anti-TB drugs and drug combinations for the intervention arm of the trial, including first-line TB drugs, third generation fluoroquinolones, ethionamide, *para*-aminosalicylic acid (PAS), cycloserine, linezolid and clofazimine, and the novel drugs, bedaquiline and delamanid. We discounted drugs if: (1) resistance was likely to be present to that drug in MDR strains (the first-line drugs) [32, 33]; (2) the drug is likely to be poorly tolerated (ethionamide and PAS); (3) the drug is associated with frequent or serious AEs (cycloserine, linezolid, clofazimine); (4) the drug is only weakly effective in killing *M. tuberculosis* (cycloserine, clofazimine, PAS); or (5) appropriate formulations are unavailable or pharmacokinetic parameters are not well understood (delamanid and bedaquiline).

We therefore decided to use a third-generation fluoroquinolone. These drugs have good efficacy against *M. tuberculosis* in vitro and are a core component of MDR-TB disease treatment regimens in both adults and children. Historically, clinicians had been hesitant to use fluoroquinolones in children following early animal research demonstrating cartilage damage in juvenile beagles [34]. However, a significant body of evidence has now demonstrated that drugs of this class are safe in children, even for long-term use [9, 35–38]. Although moxifloxacin has good efficacy against metabolically active mycobacteria, levofloxacin may have better activity against metabolically inactive mycobacteria [39]. A mouse model which evaluated a number of novel TB infection treatment regimens in a latent infection model found that levofloxacin, moxifloxacin and isoniazid had similar efficacy against drug-susceptible strains of *M. tuberculosis.* Moxifloxacin is poorly tolerated in its current formulation due to its bitter taste and there are challenges in taste masking the active ingredient [40]. In addition, the large milligram size of the tablet (400 mg) makes dosing challenging in children. Levofloxacin, in contrast, has a low tablet milligram dose, is licensed for children, has been widely used to treat paediatric MDR-TB disease and other bacterial infections, has known pharmacokinetic parameters when used at once-daily dosing [41], does not interact with antiretroviral therapy drugs and appears to have low toxicity at currently used dosages [42].

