### Trial endpoints

The primary endpoint is incident TB disease (bacteriologically confirmed or clinically diagnosed) or TB death by 48 weeks following randomisation. Incident TB and cause of death are adjudicated by an independent Endpoint Review Committee blinded to treatment allocation, based on available clinical, radiological, microbiological and molecular data using standard case definitions (see Table 1). Secondary endpoints are: (1) all-cause mortality; (b) AEs ≥ grade 3 (possibly or likely associated with drug treatment) during 24 weeks of treatment; (3) percentage of levofloxacin or levofloxacin-placebo doses ingested and retained over 24 weeks of treatment; (4) TB disease over 96 weeks; and (5) incidence of levofloxacin-resistant TB disease.

**Table 1 Tab1:** Clinical and radiological/laboratory criteria required to make a diagnosis of confirmed, probable or possible TB in child TB contacts aged < 5 years of age. Developed in collaboration with the trial teams from V-QUIN and PHOENIx

Clinical (A)	Radiological/laboratory (B)
• Cough or cervical neck mass (≥2 × 2 cm) for > 2 weeks despite a course of antibiotics • Fever or lethargy for > 1 week despite a course of antibiotics • Documented failure to thrive, i.e. flattening of weight curve crossing centiles, documented weight loss, e.g. > 5%, moderate or severe malnutrition (Weight-for-height Z score < − 2) in relation to previous measures • Classic gibbus suggestive of spinal TB • Depressed level of consciousness, new onset seizures or focal neurological signs suggestive of TB meningitis	• AFBs or caseating granulomas on microscopy (not confirmed by culture or Xpert to be TB) • CXR suggestive of TB (concurrence between two blinded CXR reviewers, with conflicts resolved by third reviewer) despite a course of antibiotics • CSF suggestive of TB (white cell count 10-500 cells per µl with a lymphocyte predominance, protein > 1 g/dL, glucose < 2.2 mmol/L) • Pleural aspirate or ascitic tap with WBC counts, protein, and glucose levels suggestive of TB, consider ADA • CT brain suggestive of CNS TB

• Confirmed TB: positive *M. tuberculosis* + at least one of either A or B

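### The only adverse-event endpoint closes at week 24, although follow-up and an efficacy endpoint run to week 96: later events are recorded but do not enter it

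*Protocol article*

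**What the plan says.** The Trial endpoints section lists one adverse-event endpoint, a secondary one: "AEs ≥ grade 3 (possibly or likely associated with drug treatment) during 24 weeks of treatment". It states no period after the last dose.

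The Adverse events section gives the matching schedule: "Safety assessments are conducted at each visit during the 24 weeks on treatment and include evaluation of symptoms, signs and laboratory investigations". For laboratory tests it adds "Safety laboratory investigations are performed at baseline and at 8, 16 and 24 weeks", with further tests at unscheduled visits if indicated. Between these come statements with no such limit: "At every study visit (and at unscheduled visits) a symptom checklist prompts for symptoms relating to possible drug toxicities", followed by evaluation of all symptomatic children by the study doctor. Later the section says "All AEs are recorded in the child’s notes and reported to the MRC CTU and ethics committees as required within agreed timescales".

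The Context and Follow-up sections give 24 weeks of treatment, a further 72 weeks of follow-up, and visits at weeks 4, 8, 12, 16, 24, 36, 48, 72 and 96. The primary endpoint runs to 48 weeks. Among the secondary endpoints, TB disease is counted over 96 weeks and all-cause mortality has no stated limit.

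The Background section poses safety as a hypothesis: "We also hypothesise that this treatment will be well tolerated, safe and cost-effective". The Choice of intervention regimen section says that clinicians had historically been reluctant to use the class in children "following early animal research demonstrating cartilage damage in juvenile beagles", and then that a substantial later body of evidence shows the class to be safe in children, including in long-term use.

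**The concern.** Benefit and harm are measured over different periods. A benefit-risk statement from the listed endpoints would set up to 96 weeks of efficacy against 24 weeks of graded, drug-attributed adverse events. An event that starts in week 25, or is first reported at the week 36 visit, is outside the adverse-event endpoint whatever its grade or attribution.

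The safety hypothesis is not restricted to the dosing period, and the Discussion expects rapid translation into policy if the drug proves effective, safe and well tolerated. The participants are child contacts under 5 without TB disease at enrolment. The Blinding section justifies the placebo partly by the need for unbiased toxicity assessment, and nothing in the article describes unblinding at week 24. A randomised comparison of later events is therefore within reach, but the adverse-event endpoint does not use it. The window is a choice that the article states, so it is not simply a detail left to the analysis plan.

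**Working it through.** **1. Timeline.** 24 weeks on treatment + 72 weeks after = 96 weeks. This agrees with the last scheduled visit, so the article is consistent on this point.

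**2. Windows side by side (Trial endpoints section).**

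| Endpoint | Stated window |
|---|---|
| Incident TB or TB death (primary) | 48 weeks |
| TB disease (secondary) | 96 weeks |
| All-cause mortality (secondary) | no limit stated |
| Adverse events of grade 3 or above, possibly or likely drug-related (secondary) | 24 weeks of treatment |

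**3. Calendar share outside the adverse-event window.** (96 − 24)/96 = 72/96 = 75% of follow-up. The visits at weeks 36, 48, 72 and 96 are 4 of 9. The first visit after the end of treatment comes 36 − 24 = 12 weeks later. These figures describe the schedule. They do not measure missed harm.

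**4. Two readings of the Adverse events section.** One sentence places safety assessments, including symptoms and signs, at visits during the 24 weeks. The next places the toxicity checklist at every study visit.

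- If the checklist runs to week 96, toxicity data are collected at four further visits but do not enter the adverse-event endpoint.
- If the first sentence governs and the checklist stops at week 24, later events depend on general questions to caregivers and unscheduled contact.

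The text does not settle which is meant. Either reading supports a clarification.

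**5. What a longer comparison could show (assumed rates only).** The article gives no adverse-event rate, so the rates below are invented for illustration.

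Sample size check: 7% v 3.5%, two-sided 5%, 80% power, pooled-variance formula without continuity correction gives 637 per arm. With design effect 1 + (2 − 1) × 0.1 = 1.1 and 10% loss, 2 × 637 × 1.1/0.9 = 1557, against 1556 stated. The stated figure reproduces, and it does not depend on the safety window.

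Effective number per arm: 778 × 0.9/1.1 = 636.5. This carries the article's intra-class correlation and loss over to adverse events at week 96, which is a further assumption.

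Power = Φ[(|p₁ − p₂| − 1.96·SE₀)/SE₁], where SE₀ uses the pooled rate and SE₁ the separate rates. Take 2% on treatment in both arms, and put any excess wholly after treatment:

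| Post-treatment, placebo v levofloxacin | Total by week 96 | Approximate power |
|---|---|---|
| 0.5% v 1% | 2.5% v 3% | 8% |
| 0.5% v 2% | 2.5% v 4% | 33% |
| 1% v 3% | 3% v 5% | 44% |

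Last row in full: SE₀ = √(2 × 0.04 × 0.96/636.5) = 0.01099; SE₁ = √((0.03 × 0.97 + 0.05 × 0.95)/636.5) = 0.01097; (0.02 − 1.96 × 0.01099)/0.01097 = −0.14; Φ(−0.14) = 0.44.

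In each scenario the 24-week endpoint shows no difference by construction. The week 96 comparison is underpowered as a test, so its value is in estimation.

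**The case against.** An on-treatment window is a coherent and common choice for an endpoint restricted to events attributed to the drug. This stands: the window is not an error in itself.

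A reader might infer that events after week 24 cannot count against safety at all. The article does not support that. The checklist is described for every study visit, all adverse events are recorded and reported, deaths count without a 24-week limit, and an Independent Data Monitoring Committee sees unblinded data. Nothing bars reporting later events by arm. They are outside one endpoint, not outside the trial's data.

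A reader might also infer that the window is set against an open concern about late joint injury. The article presents the cartilage finding as historical and answered by later evidence, and it says nothing about when joint events begin. Nor can the 75% calendar share be read as 75% of harm missed.

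Finally, the article condenses a full protocol that is not at hand, and the schedule of evaluations figure is not shown. Either may settle what is assessed at weeks 36 to 96, and the analysis plan may already tabulate later events. This also stands, and it limits the point to the published endpoint definition and the unclear wording. The endpoint window itself is fixed in the article, so the mismatch with the untimed safety hypothesis remains.

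**Conclusion.** The point holds in a limited form. The only adverse-event endpoint ends with treatment, with no lag, while efficacy is counted to 48 and 96 weeks and the safety hypothesis has no time limit. As defined, that endpoint supports a conclusion about safety during treatment. A conclusion beyond the last dose would have to rest on mortality and on whatever is reported outside the endpoint. The Adverse events section also leaves unclear whether symptom assessment continues after week 24.

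The size of the effect cannot be stated, because the documents give no adverse-event rate and no onset pattern. The illustrative powers of 8% to 44% rest wholly on assumed rates. This is an inexpensive improvement to the plan, not a flaw that undermines the trial. It assumes that the full protocol and analysis plan do not already provide the by-arm reporting described under the fix.

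**What to change.** - Keep the 24-week endpoint unchanged.
- Add a supplementary comparison by arm of adverse events with onset from randomisation to week 96, split by onset on or after treatment, with musculoskeletal events of any grade shown separately. Present estimates with confidence intervals that allow for household clustering, not a powered test. Specify it before any data by arm are seen.
- Reconcile the two statements in the Adverse events section so that symptom assessment at the week 36, 48, 72 and 96 visits is explicit.
- If this is not done, limit the safety conclusion to the treatment period.
- Wherever musculoskeletal reporting is explained, describe the cartilage concern as historical, as the article does.

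The cost is slightly more data entry and more background childhood events, which dilute any drug effect but should be balanced by randomisation. No visits or laboratory tests are added. Recruitment began in September 2017, so some children may already have passed week 24. How complete their later data are depends on which reading of the Adverse events section the sites have followed.
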